### Subgroup analyses

Exploratory subgroup analyses will be performed for cognitive motor and language composite scores assessed by Bayley III at 3 and 12 months. Subgroup (main effect) and the subgroup-by-treatment-by-visit interaction (as well as subgroup-by-treatment and subgroup-by-visit interaction) terms will be added to the constrained longitudinal data analysis model to evaluate whether the treatment effect differs between subgroup categories. The following subgroups will be explored: sex (male/female), baseline anaemia status (yes/no), baseline iron deficient status (yes/no), baseline iron deficient anaemia status (yes/no), baseline stunting (yes/no), baseline home stimulation as measured by the family care indicator questionnaire (below/ above median family care indicator total score), baseline household food insecurity status (yes/no), baseline wealth status (below/ above median wealth index score), and union (Bhulta, Golakandail, Rupganj). No multiplicity adjustments are planned for the subgroup analyses due to their explorative nature, we will present the estimates and two-sided 95% confidence interval along with (multiplicity unadjusted) P-Values. Results of the subgroup analyses will be displayed using Forest plots.

### Changes from the registry and published study protocol

This paper includes changes to the statistical analysis plan of the BRISC trial in the registry (registered May 2017) and protocol paper (accepted September 2017). These changes are:

The register states that the regression models will incorporate key confounders and unbalanced baseline factors into the model. Instead, the primary analysis model will include the stratification factors used during the randomisation and additional models (sensitivity analyses) will incorporate key confounders, or key confounders and unbalanced baseline factors. The protocol states on the topic of:Multiple testing: We detailed a multiple testing procedure for the primary and key secondary outcomes, thus the confidence level for the associated two-sided confidence interval will be less than 5% for some treatment effects.Analysis of binary outcomes: We changed the analysis model from generalised estimating equations to a mixed model.

This paper documents version 1 of the statistical analysis plan dated April 20, 2020. Any changes to this version between publishing and breaking of the code will be tracked and still considered as planned analyses. The statistical analysis plan will be approved during the blinded data review before breaking of the allocation code. Any changes after this signed version will be considered post-hoc.

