### Sample size

The sample size for the trial was to recruit 3300 children (1100 per treatment arm) in order to have 80% power to detect a two-point difference in Bayley III composite cognitive score between the iron supplementation and placebo arm and the MNPs and placebo arm (two-sided 2.5% level of significance per comparison), assuming a standard deviation of 15 and a 20% loss to follow up after 3 months of intervention. No interim analyses to stop the trial early were planned, and no interim analysis was conducted.

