### Efficacy (including selected laboratory) outcomes: analysis

A constrained longitudinal data analysis method proposed by Liang and Zeger
^
16
^ will be used to examine the primary outcome (Bayley III cognitive composite score at baseline, 3 months and 12 months post-baseline). The model will incorporate study visit as a categorical variable, treatment and treatment by study visit interaction and adjust for the stratification randomisation factors (union and sex) as main effects. The model will assume a common baseline mean across the three treatment arms and an unstructured variance-covariance among the repeated measurements. In case of non-convergence, we will consider alternative structures (first-order autoregressive, Toeplitz, compound symmetry). The treatment effect will be estimated from this model as the difference between two treatments in mean change from baseline to 3 months post-intervention (
Table 2).

**Table 2. T2:** Primary, key secondary, and secondary outcomes, according to treatment group (intention-to-treat population).

Assessment	Iron (N=XXXX)		MNPs (N=XXXX)		Placebo (N=XXXX)		Iron vs. Placebo			MNPs vs. Placebo			Iron vs. MNPs		
	no. of children measured	Mean (SD) *	no. of children measured	Mean (SD) *	no. of children measured	Mean (SD) *	Estimate (CI) †	P Value Unadjusted	P Value Adjusted †	Estimate (CI) †	P Value Unadjusted	P Value Adjusted †	Estimate (CI) †	P Value Unadjusted	P Value Adjusted †
Month 3															
Primary endpoint															
Bayley score															
Change in cognitive composite score	XXXX	X.X (X.X)	XXXX	X.X (X.X)	XXXX	X.X (X.X)	X.X (X.X to X.X)	0.XXX	0.XXX	X.X (X.X to X.X)	0.XXX	0.XXX	X.X (X.X to X.X)	0.XXX	0.XXX
Key secondary endpoints															
Bayley score															
Change in language composite score	XXXX	X.X (X.X)	XXXX	X.X (X.X)	XXXX	X.X (X.X)	X.X (X.X to X.X)	0.XXX	0.XXX	X.X (X.X to X.X)	0.XXX	0.XXX	X.X (X.X to X.X)	0.XXX	0.XXX
Change in motor composite score	XXXX	X.X (X.X)	XXXX	X.X (X.X)	XXXX	X.X (X.X)	X.X (X.X to X.X)	0.XXX	0.XXX	X.X (X.X to X.X)	0.XXX	0.XXX	X.X (X.X to X.X)	0.XXX	0.XXX
Anthropometric indices															
Change in length-for-age z-score	XXXX	X.X (X.X)	XXXX	X.X (X.X)	XXXX	X.X (X.X)	X.X (X.X to X.X)	0.XXX	0.XXX	X.X (X.X to X.X)	0.XXX	0.XXX	X.X (X.X to X.X)	0.XXX	0.XXX
Change in weight-for-age z-score	XXXX	X.X (X.X)	XXXX	X.X (X.X)	XXXX	X.X (X.X)	X.X (X.X to X.X)	0.XXX	0.XXX	X.X (X.X to X.X)	0.XXX	0.XXX	X.X (X.X to X.X)	0.XXX	0.XXX
Laboratory indices															

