### Missing data handling

To describe the missing data, the frequency and percentage of children with missing data at baseline, month 3 and month 12 will be summarised for the child development, anthropometry, and laboratory outcomes. In addition, baseline and demographic characteristics will be summarized by those with and without missing data for the cognitive composite score (at baseline, month 3, and month 12) to explore the missing data assumption and identify any variables not included in the target analyses that are potentially associated with missingness (known as auxiliary variables).

As the primary strategy to handle missing data, the analysis will use a likelihood-based approach. This approach relies on the underlying assumption that the probability of missing outcome data is not related to the missing data but to some of the observed measured data in the model (Missing At Random [MAR]). 

As the secondary strategy (sensitivity analysis), missing data on the outcomes will be multiply imputed using chained equations. The imputation model will include union, sex, visit (categorical), the family care indicator total score (continuous), maternal education (continuous), all variables listed as specified for subgroup analyses, and it will be performed separately by treatment group. In addition, auxiliary variables identified during the blinded data review meeting may be included. The variables with missing data will be imputed using a linear regression model if continuous and logistic regression if binary, whereby ferritin will be log
_e_ transformed prior to imputation as this outcome will be log
_e_ transformed in the analysis of interest. The missing outcome data at baseline, 3-month and 12-month visits will be imputed using the “just another variable” approach (also known as imputing in wide format) which requires a separate imputation model for imputing the variable at each assessment time. The number of imputed data sets will be greater than or equal to the percentage of missing data in the available case analyses. The imputed data sets will be analysed using the models described. The estimates from the analyses of the imputed data sets will be combined to obtain a pooled common estimate and corresponding confidence interval using Rubin’s rules. For the above standard implementation of multiple imputation, we have assumed the outcome data are MAR.

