### Sensitivity analyses

In addition to the analyses specified for the primary, key secondary, and secondary outcomes, the following sensitivity analyses will be applied for these outcomes:

1. Analyses consisting of models adjusted for potential prognostic or predictive variables:

a. Adding to the model adjusted for union and sex, the main effect of family care indicator score (continuous) and maternal education (No education; 1–8 years schooling completed; 9–12 years schooling completed; >12 years schooling completed).b. Adding to the model adjusted for union and sex, the main effect of variables in
Table 1 demonstrating unexpected imbalance between the treatment arms after unblinding.c. Adding to the model adjusted for union and sex, the main effect for rater and the interaction between rater and study visit (only applies to Bayley III, Wolke’s Behaviour rating scale, and temperament questionnaire).d. Adding to the model adjusted for union, sex, family care indicator, and maternal education, the main effect for rater and the interaction between rater and study visit (only applies to Bayley III, Wolke’s Behaviour rating scale, and temperament questionnaire).

2. Analyses of the secondary strategy to handle missing data.

3. Analyses of the model adjusted for union and sex for the per-protocol population defined as randomised children who were compliant to treatment, and without protocol violations (no informed consent or withdrawn informed consent for use of all data, violation in/ exclusion criteria, or improper unblinding of the child’s allocated treatment).

4. Analyses using the Complier Average Causal Effect method to estimate the average effect of treatment among compliers
^
17
^.

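### The primary cognition model is valid, but it leaves two baseline covariates that the plan lists as potentially prognostic to sensitivity models, so their precision cannot reach the two deciding comparisons

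*SAP article*

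**What the plan says.** Under the efficacy analysis heading, the primary outcome is analysed with a constrained longitudinal model that has visit, treatment and their interaction, a common baseline mean and an unstructured covariance. Its only other covariates are the randomisation strata: the model will "adjust for the stratification randomisation factors (union and sex) as main effects". The baseline cognitive score is one of the repeated outcomes, so the model already uses it.

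Family care indicator score and maternal education are listed among the baseline data under outcome variables. They enter model 1a of the sensitivity analyses, and 1d together with rater effects, under the description "Analyses consisting of models adjusted for potential prognostic or predictive variables". The imputation model in the missing data section also names them: "the family care indicator total score (continuous), maternal education (continuous").

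The section on changes records that the registry had put key confounders and unbalanced baseline factors in the regression models, and then says "Instead, the primary analysis model will include the stratification factors used during the randomisation and additional models (sensitivity analyses) will incorporate key confounders". It gives no reason for the change.

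Under the multiple testing section, two comparisons with placebo are tested at two-sided 2.5% each. Success on either meets the primary objective. The iron-versus-MNPs test and the Hochberg tests of the key secondary outcomes open only through these results.

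**The concern.** In a linear model under randomisation, adjusting for named, pre-randomisation covariates that predict the outcome lowers the residual variance and leaves the type I error intact. The plan has two candidates in hand and gives them a role in adjustment, in imputation and, for home stimulation, in a subgroup analysis. It does not use them in the one model that feeds the decision rule. If model 1a gives a narrower interval, that interval cannot reject a primary hypothesis or open a later gate.

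At stake is precision only: the width of the primary intervals and the chance of detecting the planned two-point difference. This has some practical weight because power is not in surplus on the plan's own sample size inputs.

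**Working it through.** **Inputs from the sample size section.** The plan sets out to "recruit 3300 children (1100 per treatment arm"), with "80% power to detect a two-point difference in Bayley III composite cognitive score", a "two-sided 2.5% level of significance per comparison", and "assuming a standard deviation of 15 and a 20% loss to follow up after 3 months of intervention". Evaluable children per arm: 1100 × 0.8 = 880.

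**The plan's own figure first.** n per arm = 2 × (z₁ + z₂)² × 15² / 2², with z₂ = 0.8416 for 80% power.
- At two-sided 2.5% (z₁ = 2.2414): 1070 evaluable per arm, and 1070/0.8 = 1338 recruited. This does not reproduce 1100.
- At two-sided 5%: 883 evaluable and 1104 recruited. This does.
- Power with 880 per arm at 2.5%: SE = 15 × √(2/880) = 0.715; Φ(2/0.715 − 2.2414) = 71.1%.

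The 71.1% is the starting point before any variance reduction. It comes from the sample size calculation, not from the choice of covariates.

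**Assumed inputs.** The documents give no correlation and no R-squared. Let ρ be the correlation between baseline and month-3 cognitive score (0.2, 0.3, 0.5). Let a be the R-squared of the two covariates with the score, taken as equal at both visits (0.02, 0.05, 0.10). SD 15 is used as the spread before these terms, with no credit for union and sex.

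**Formulas.**
- Variance explained by the baseline score alone: R₀ = ρ².
- Variance explained by baseline score and covariates together: R₁ = (a + ρ² − 2aρ)/(1 − a). This allows for the part of the covariate effect that the baseline score already carries.
- Power = Φ(2 / [15 × √(2/880 × (1 − R))] − 2.2414).

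**One case in full (ρ = 0.3, a = 0.05).**
- Baseline score only: R₀ = 0.09, SE = 0.682, power = Φ(2.932 − 2.241) = 75.5%.
- With covariates: R₁ = (0.05 + 0.09 − 0.03)/0.95 = 0.116, SE = 0.672, power = Φ(2.974 − 2.241) = 76.8%.
- The SE falls by 1.4% and power rises by 1.3 points.

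**All cases, power per comparison (SE reduction in brackets).**

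| ρ | Baseline score only | a = 0.02 | a = 0.05 | a = 0.10 |
|---|---|---|---|---|
| 0.2 | 73.0% | 73.7% (0.7%) | 74.7% (1.8%) | 76.6% (3.8%) |
| 0.3 | 75.5% | 76.0% (0.5%) | 76.8% (1.4%) | 78.3% (3.0%) |
| 0.5 | 83.8% | 84.1% (0.3%) | 84.5% (0.9%) | 85.3% (1.9%) |

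The gain runs from about 0.3 to 3.6 points. At a = 0.15 and ρ = 0.2 it would reach about 5.7 points (73.0% to 78.7%).

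**The case against.** The strongest reply is that the plan contains no error here. The primary model is fully specified, adjusts for both stratification factors and uses the baseline cognitive score. The adjusted model is pre-specified as 1a, and the change from the registry is declared. Which of two valid models is primary is partly a matter of judgement. All of this stands, and it makes the point an improvement rather than a correction.

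Five stronger readings might be inferred, and the documents do not support them.
- *The plan treats these variables as established predictors.* It says potential prognostic or predictive, under a heading that also covers rater effects and imbalances found after unblinding.
- *A single test decides the trial.* There are two primary comparisons, and either suffices.
- *The primary missing-data assumption is left exposed.* The primary likelihood analysis does not condition on the two variables, but the pre-specified multiple imputation analysis does. The plan does not say that they predict missingness.
- *The gain is larger.* If the covariates explained 2, 5 or 10% of the variance left after the baseline score, power at ρ = 0.3 would go from 75.5% to 76.4, 77.8 or 80.2%. That ignores overlap: home stimulation and maternal education plausibly affect the baseline score too.
- *Leaving the registry's approach was a mistake.* Nothing shown says that the registry's key confounders were these two variables. Moving adjustment for observed imbalance out of the primary model was sound.

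The change also comes after follow-up has ended. This is acceptable only while the allocation code is unbroken.

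**Conclusion.** The point holds as a modest, low-cost gain in precision. The current primary analysis is valid and unbiased, with no inflation of type I error. Two covariates already in hand are kept out of the model behind the two primary comparisons and their gates.

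On the assumptions shown, the benefit is about 0.3 to 3.6 power points per comparison for a covariate R-squared of 0.02 to 0.10. It shrinks as the baseline score becomes more predictive. The size rests on assumed values of ρ and a, and on equal association at both visits. If the covariates turn out to be weakly prognostic, the gain is close to nil.

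A reader might infer that the omission explains why the stated inputs give 71.1% rather than 80% power. It does not. That gap is a separate matter of the sample size and the 2.5% level, and in most of the cases above the two covariates would not close it.

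**What to change.** Before the allocation code is broken:
- Add family care indicator score (continuous) and maternal education (in the categories of model 1a) to the primary model, each with its interaction with visit. Model 1a has main effects only, which capture the full gain only if the covariate effects are similar across visits.
- Keep the union-and-sex model as the pre-specified sensitivity analysis in place of 1a.
- Leave covariates chosen for imbalance after unblinding (1b) out of the primary model.
- State a simple single-imputation rule for missing values of the two covariates.

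The SAP article counts tracked changes made before code-breaking as planned; after the signed version they would be post hoc. The cost is SAP wording, a few more model terms and a rule for what should be rare missing covariate values. If the sponsor prefers the present model, a sentence giving the reason would be enough.

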## Discussion

Iron interventions in early childhood are recommended as an effective intervention to reduce the prevalence of anaemia and improve child development. However, robust evidence for the effects of iron on child development and, importantly, its possible risks is lacking. The BRISC trial will provide definitive evidence for the effects of universal provision of iron, in the form of iron syrup and iron-containing MNPs (the WHO recommendations) on child development, growth, anaemia, and morbidity both immediate and medium term. If effective, it may also establish whether iron supplements or MNPs are better. The results of this rigorous randomised controlled trial will influence global policy guidelines and programmatic practices around universal iron interventions in infants and young children. 

## Data availability

No data are associated with this article.
